### Who will take informed consent? {26a}

The principal investigator and research staff who have completed all relevant training to understand the protocols and safety requirements of the COG-EYE study will obtain written informed consent. Participants who can provide informed consent by themselves will be recruited. Separate information sheets and consent forms will be provided to the participants and caregivers.

### Additional consent provisions for collection and use of participant data and biological specimens {26b}

Participants will be encouraged to consent for sharing anonymized demographic data with collaborators and colleagues.

### Interventions

#### Explanation for the choice of comparators {6b}

We expect that it may be difficult to observe significant changes in cognitive scores or the clinical dementia rating scale over 12 weeks. Therefore, more sensitive surrogate markers, including eye-tracking metrics and digital pen data, should be employed to measure subtle changes in cognition. Eye-tracking metrics such as fixation, saccade, and smooth pursuit are correlated with MMSE scores [10], standard visuospatial test scores [11], and cortical thickness [12], respectively.

#### Intervention description {11a}

Donepezil is not approved for the treatment of MCI due to AD; no ChEI has been approved for its treatment. A dose of donepezil at 10 mg once daily is well established in clinical practice for patients with dementia. In trials, patients with MCI generally receive donepezil at a dose of 5–10 mg daily [6]. The proposed dose for donepezil of 10 mg once daily is due to the titration schedule. Thus, trials of donepezil in patients with MCI begin with the administration of donepezil 5 mg once per day.

We plan to recruit 78 participants (39 in each arm) for a randomized, open-label study, as illustrated in the trial flowchart in Fig. 1. The study duration will be 12 weeks, and in total, there will be six scheduled follow-ups with the investigators. The dates of all visits and assessments will be recorded for all the participants. The schedule of the trial procedures and visits are provided in Fig. 2.

**Fig. 1 Fig1:**
[figure not shown]
Flowchart of the COG-EYE study. MCI, mild cognitive impairment; PET, positron emission tomography

**Fig. 2 Fig2:**
[figure not shown]
COG-EYE schedule of enrolment, interventions, and assessments**.** CDR, Clinical Dementia Rating; ECG, echocardiography; GDS, Global Deterioration Scale; MMSE, Mini-Mental State Examination; MRI, magnetic resonance imaging; PET, positron emission tomography; S-IADL, Seoul-Instrumental Activities of Daily Living; TC, telephone consultation; V, visit; VOSP, visual object and space perception battery

During the screening visit, blood samples (for analyses of thyroid function, folic acid, and vitamin b12; syphilis screening; and apolipoprotein E genotyping), echocardiography (ECG), neuropsychological test battery, brain MRI, and amyloid PET will be collected. These results are needed to screen for other causes of cognitive impairment and to only recruit patients with MCI in the Alzheimer’s continuum.

Allocation will occur after baseline screening. Donepezil will be packed with clear dosing instructions and schedule. At visit 1, detailed baseline assessments will be required of all participants. Then, participants allocated to the donepezil group will be instructed to consume a dose of 5 mg once daily for the first 4 weeks. The participants allocated to the control group will not be administered donepezil during the study period. At visit 2, follow-up assessments of the measures of efficacy, except for VOSP, and detailed reporting of potential adverse effects will be required of all participants. Participants allocated to the donepezil group will then be instructed to increase the dose to 10 mg once daily for the next 8 weeks. At visit 3, follow-up assessments, including all measures of efficacy performed at baseline, and detailed reporting of potential adverse effects will be required of all participants.

V1, V2, and V3 measurements will be acquired with the following means.1. Eye-tracking metrics during the simplified RCFT and CDT on a digital tablet.2. MMSE3. CDR4. GDS5. S-IADL6. VOSP (VOSP is not performed at V2).7. Digital pen data during simplified RCFT copying test on digital tablet [13]

We modified the original RCFT to a simpler version and validated our simplified RCFT against the original RCFT in a previous study [13]. To evaluate subtle differences, we will measure eye-tracking metrics and digital pen data during copying and determine whether these digital data are useful as surrogate markers for evaluating visuospatial dysfunction. CDT is one of the most widely used screening tests for AD, and digital CDT has recently been introduced [14, 15]. We will also measure eye-tracking metrics and digital pen data while participants perform the digital CDT (Fig. 3).

**Fig. 3 Fig3:**
[figure not shown]
Drawing from the simplified RCFT and CDT. **A** The upper half is defined as the “perceptual space” (blue color), and the lower half is defined as the “working space” (red color). **B** The ring shaped AOI (green color) is defined as the “numbers” and the V-shaped AOI (yellow color) is defined as the “hands” of the clock drawing. We will measure eye-tracking metrics including fixations, saccades, and switches between the two AOIs. AOI, area of interest; CDT, clock drawing test; RCFT, Rey-Osterrieth Complex Figure

Participants and caregivers will be required to assess the MMSE, CDR, GDS, and S-IADL during the study to check general cognition and clinical stage. The VOSP consists of eight tests to assess object and space perception. In this study, participants will perform only four tests of VOSP with space perception (test 5: dot counting; test 6: position discrimination; test 7: number location; test 8: cube analysis), because tests with object perception will be difficult for our participants to understand due to cultural differences.

A safety check will be conducted at weeks 1, 4, 5, 12, and 13. At week 1, there will be a telephone consultation about side effects after taking 5 mg of donepezil for 1 week. At week 4, participants and caregivers will be required to attend the clinical research site for detailed assessment of potential adverse effects. At week 5, there will be a telephone consultation regarding side effects after an increase to 10 mg donepezil for 1 week. If a participant has any side effect to 10 mg of donepezil, the participant will continue to take 5 mg of donepezil until week 12. At week 12, participants and caregivers will be required to attend the clinical research site for detailed assessments, including all measures of efficacy performed at baseline and detailed reporting of potential adverse effects. At week 13, there will be a telephone consultation after completing all protocols.

#### Criteria for discontinuing or modifying allocated interventions {11b}

Study intervention may need to be discontinued or modified due any of the following reasons.1. Allergic reaction to the medication.2. An adverse event which requires discontinuation of the trial medication or results in inability to continue to comply with trial procedures.3. Violation of inclusion/exclusion criteria or significant protocol violation.4. Withdrawal of consent.5. Significant nonadherence to treatment regimen or trial requirements6. The investigator determines that the participant has to discontinue.

In the case of withdrawal from the clinical trial, the administration of the medication should be stopped, and the date of discontinuation, reasons, and findings should be recorded in the CRF, along with all the results of the trial obtained until the time of withdrawal. In the case of exclusion from clinical trials due to clinically significant laboratory abnormalities, follow-up will be conducted for a period determined to be reasonable or until the relevant event or laboratory abnormality is resolved.

#### Strategies to improve adherence to interventions {11c}

To improve adherence to intervention protocols, there will be a telephone consultation after taking the first dose for 1 week and increasing the dose for 1 week. Tablets will be counted upon return to clarify compliance with the planned dosing.

### Relevant concomitant care permitted or prohibited during the trial {11d}

#### Permitted medication

In the event of other diseases or adverse reactions, medications will be permitted under the judgment of the clinician, but all medications and reasons for administration will be recorded in the CRF of the participants.

#### Prohibited medication

 The medications to be prohibited during the clinical trial period are as follows; if a participant uses contraindicated medications, participation in the clinical will be stopped.1. Other ChEIs: rivastigmine, galantamine.2. NMDA receptor antagonist: memantine.

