### Outcomes {12}

#### Primary

1. Changes in the ratio of the number of fixations between the two AOIs (working space/perceptual space) performed by the simplified RCFT from baseline to 12 weeks (Fig. 3).

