## Assignment of interventions: blinding

### Who will be blinded {17a}

COG-EYE is an open-label trial; thus, participants, caregivers, principal investigator, and staff will not be blinded.

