### Plans to promote participant retention and complete follow-up {18b}

Participants will be in close contact with each other. There will be scheduled safety checks and frequent contact with the research staff as per the participants’ wish. All randomized participant data will be included in the analysis. If participants withdraw from the study at any stage, they will be asked whether their data accumulated at the point of withdrawal could be included.

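### The prohibited-medication rule ends trial participation rather than the drug, so a participant stopped before week 12 has no measured primary outcome

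*Protocol article*

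**What the plan says.** All references are to the protocol article.

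- **Prohibited medication ({11d}).** Rivastigmine, galantamine and memantine are barred during the trial, and "if a participant uses contraindicated medications, participation in the clinical will be stopped". The rule is mandatory, covers both arms, and ends participation rather than only the study drug.
- **Criteria for discontinuing or modifying ({11b}).** On withdrawal the medication is stopped and the date, reasons and findings go into the CRF, "along with all the results of the trial obtained until the time of withdrawal". Follow-up after exclusion is described only for laboratory abnormalities.
- **Participant retention ({18b}).** Data from every randomized participant are to enter the analysis. Of those who withdraw, "they will be asked whether their data accumulated at the point of withdrawal could be included".
- **Outcomes ({12}), Primary.** The endpoint is the change in the fixation ratio "performed by the simplified RCFT from baseline to 12 weeks".
- **Intervention description ({11a}), text after Fig. 2.** There is one intermediate measurement: "At visit 2, follow-up assessments of the measures of efficacy, except for VOSP", which the text after Fig. 3 places at week 4.
- **Intervention description ({11a}), text after Fig. 3.** After a side effect on 10 mg, "the participant will continue to take 5 mg of donepezil until week 12", and the week-12 assessments follow as usual.
- **Who will be blinded ({17a}).** "participants, caregivers, principal investigator, and staff will not be blinded".

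**The concern.** Use of another anti-dementia drug happens after randomization. Ending participation when it happens turns a departure from planned treatment into a missing primary outcome. Everyone knows the allocation and controls receive no donepezil, so whether such a drug is started may depend on how the participant is doing and on the arm. The week-12 values lost may then be a selected set, and selected differently in the two arms. A t-test on the remaining participants would no longer compare the groups as randomized.

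The week-4 measurement is only a partial safeguard. It precedes the 8 weeks at 10 mg, and anyone stopped before visit 2 has a baseline value alone. An analysis plan can choose how to treat missing values, but it cannot recover a measurement that the protocol's own rule prevented.

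**Working it through.** **1. Tracing a stopped participant through the protocol.**

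| Time of stop | Eye-tracking available | Primary outcome |
|---|---|---|
| Before visit 2 (week 4) | Baseline | Not measured |
| After visit 2, before week 12 | Baseline, week 4 | Not measured |

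Sections {11b} and {18b} do not forbid a later assessment, but neither provides for one. Section {20c} says missing data will be sought where possible, but it schedules no visit for someone whose participation has ended. The aim in {18b} of analysing all randomized participants cannot be met for the week-12 change in these people.

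**2. The plan's own figures (Sample size {14}).** Inputs: standardized effect d = 0.8, two-sided alpha 0.05, two-sample t-test, 90% power, 12% attrition. From the noncentral t distribution, 33 per arm gives power 0.893 and 34 gives 0.902, so 34 is the minimum. Then 34 / (1 − 0.12) = 38.6, rounded up to 39 per arm and 78 in total. Both figures reproduce. With all 39 per arm observed, power is 0.937.

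**3. Effect of stopping, on an assumed range.** The documents give no rate of prohibited-drug use. Assume k = 1, 2 or 4 of 39 controls are stopped, nobody else is lost, and the stopped controls would have been s SD worse at week 12 than the remaining controls. The mean of all 39 controls lies s × k/39 below the mean of those observed, so the treatment difference is understated by s × k/39. For example, 1 × 4/39 = 0.103, and 0.103/0.8 = 13%.

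| k | s = 0 | s = 0.25 | s = 0.5 | s = 1 |
|---|---|---|---|---|
| 1 | 0 | 0.006 | 0.013 | 0.026 |
| 2 | 0 | 0.013 | 0.026 | 0.051 |
| 4 | 0 | 0.026 | 0.051 | 0.103 |

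The same losses in the donepezil arm would overstate the difference by the same amounts.

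**4. Power if stopped.** 39 against 39 − k, with d = 0.8 − s × k/39:

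| k | s = 0 | s = 0.25 | s = 0.5 | s = 1 |
|---|---|---|---|---|
| 1 | 0.934 | 0.930 | 0.926 | 0.918 |
| 2 | 0.931 | 0.923 | 0.915 | 0.896 |
| 4 | 0.924 | 0.907 | 0.887 | 0.840 |

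**5. Power if kept and measured.** 39 against 39. Let f be the share of the 0.8 effect that the other drug gives an exposed control, so d = 0.8 × (1 − f × k/39):

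| k | f = 0 | f = 0.5 | f = 1 |
|---|---|---|---|
| 1 | 0.937 | 0.931 | 0.925 |
| 2 | 0.937 | 0.925 | 0.911 |
| 4 | 0.937 | 0.911 | 0.879 |

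At f = 1, d falls by 0.8 × k/39, which is 0.02, 0.04 or 0.08. That is an upper bound, and nothing in the documents supports it for memantine. Against f = 1, stopping has the lower power only when s exceeds about 0.60, for each k. Power therefore does not settle the matter. The argument is selective loss of the primary outcome.

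**The case against.** - **The article is condensed.** Assessments after withdrawal may be described in the full protocol, which {31c} promises as a supplement and which is not shown. That would answer a complaint about omission alone. This concern starts from a stated rule that participation ends, and nothing in the article softens it.
- **The trigger is unlikely.** Of MCI due to AD the protocol says "no ChEI has been approved for its treatment". The Discussion adds that guidelines do not recommend these drugs in MCI, entry excludes recent users, and follow-up is 12 weeks. This stands. The 13% figure needs about 10% of controls (4 of 39) to start such a drug and a full 1 SD of selection, and the documents support neither. With one control stopped the shift is at most 0.026 SD, about 3% of 0.8. The attrition allowance covers up to 5 losses per arm, though it covers numbers and not selective loss.
- **Selection is assumed.** Section {6b} expects little visible cognitive change over 12 weeks, which weakens the idea that decline would prompt prescribing. This also stands as a limit on size.
- **Keeping exposed controls can move the estimate more than stopping them.** At f = 1 this holds for s of 0, 0.25 and 0.5. Whether it counts as distortion depends on the estimand. A measured week-12 value leaves every estimand available, whereas stopping rules out analysing all randomized participants.
- **The contrast with the 5 mg step-down is imperfect, and other withdrawal routes in {11b} lose week-12 data too.** Both points are fair. The step-down stays within the assigned treatment, and the change proposed here closes one route only.

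**Conclusion.** The concern holds as a design choice worth changing. Followed as written, the rule leaves the week-12 primary outcome uncollected after a post-randomization event that may relate to outcome and arm, and this sits badly with the stated intention to analyse all randomized participants. No figure in the plan is wrong. The likely effect is small: from nothing to 0.103 SD on an assumed range of 1 to 4 controls stopped and 0 to 1 SD of selection, in either direction depending on the arm affected. Confidence is medium, because the frequency of the event and the strength of selection are both unknown.

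**What to change.** In Prohibited medication ({11d}), replace the clause that ends participation with wording such as:

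*Use of a prohibited medication will be recorded as a protocol deviation. The prohibited drug, or study donepezil, will be stopped where safety requires. The participant will remain in follow-up and complete the week-12 eye-tracking assessment unless consent is withdrawn. The number of participants exposed will be reported by arm.*

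Optionally, and only together with this change, add donepezil other than the assigned study medication, in either arm, to the list.

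The cost is one sentence. The week-12 visit and the CRF medication record already exist. The downside is possible dilution from exposed participants who stay in the primary comparison: at the f = 1 upper bound, power falls from 93.7% to 92.5%, 91.1% or 87.9% with 1, 2 or 4 exposed controls, and there is no dilution if the other drug has no effect. Trial status describes recruitment as ongoing, so the change is an amendment to the MFDS and the IRB under {25}, and it cannot recover anyone already stopped.

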### Provisions for post-trial care {30}

Since it is important for patients with MCI to follow-up for checking the cognitive decline, it is recommended that participants undergo annual cognitive evaluations after clinical trials.

### Outcomes {12}

#### Primary

1. Changes in the ratio of the number of fixations between the two AOIs (working space/perceptual space) performed by the simplified RCFT from baseline to 12 weeks (Fig. 3).

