## Trial design {8}

The COG-EYE is a randomized, open-label, parallel design, superiority trial with a 1:1 allocation ratio to evaluate the efficacy of donepezil in improving visuospatial abilities in patients with MCI.

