### Sample size {14}

The sample size was calculated to test differences in the primary outcome between the donepezil and control groups based on the standardized effect size commonly used in clinical studies on cognitive impairment [16, 17]. The standardized effect of donepezil on cognitive tests scores was reported as medium to large size (0.3 ~ 1.9) [18–21]. A recent study showed that fixation frequency had a large effect size (0.8) for the difference between apathetic and non-apathetic AD [22]. This suggests that eye-tracking metrics, such as fixation, might be more sensitive than cognitive scores; therefore, a large standardized effect can be expected in this trial.

A sample size of 34 patients per group achieved 90% power to detect a standardized effect size of 0.8 with a significance level of 0.05, using a two-sided two-sample *t*-test. The standardized effect size of this study was set as the lower bound of the large effect size range (> 0.8) using a conservative approach. Assuming an attrition rate of 12%, a total sample size of 78 (39 patients per group) should be enrolled. The sample size was calculated using PASS 22.0.2.

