## Statistical methods

### Statistical methods for primary and secondary outcomes {20a}

As the trial has a parallel design, all analyses will be performed for comparison between the donepezil and control groups. The primary outcome will be analyzed using the two-sample *t*-test, the continuous secondary outcome will be analyzed using the two-sample *t*-test or Mann–Whitney *U* test according to normality, and the ordinal secondary outcome will be analyzed using the Mann–Whitney *U* test. An analysis adjusting for the baseline value will also be performed for each outcome. All results will be presented as mean, median, standard deviation, interquartile range, minimum maximum, and 95% confidence intervals. Sensitivity analyses will be performed to report the robustness of the data.

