## Discussion

Current guidelines do not recommend using ChEIs in patients with MCI because of the lack of evidence [5, 23, 24]. This trial begins with the question of what if we narrow participants to only MCI with AD biomarkers and use a surrogate marker that could show subtle changes instead of conventional cognitive tests or clinical rating scores. In this context, we aim to investigate whether donepezil improves visuospatial dysfunction in patients with amyloid PET-positive MCI using eye-tracking metrics.

In terms of surrogate markers, studies in patients with MCI have used neuroimaging markers as primary outcome measures, such as atrophy of the hippocampus [25], regional cortical thickness, and basal forebrain [26, 27]. Neuroimaging requires a relatively long time interval to measure changes before and after treatment, whereas eye movements immediately reflect changes in the cognitive processes underlying behavioral outcomes. Over the past decades, studies have shown that eye-tracking measurements are useful for assessing subtle cognitive processes [28–30]. Eye-tracking metrics such as fixation, saccade, and smooth pursuit are correlated with MMSE scores [10], standard visuospatial test scores [11], and cortical thickness [12], respectively. Recently, a study showed that fixation time and frequency were reduced on social images in apathetic patients with AD [22]. Another study showed that patients with AD need longer reaction times and are less efficient at detecting hazards [31, 32]. Moreover, our group reported that the increased number and duration of fixations might reflect more cognitive efforts to compensate for the lack of visual perception in patients with AD [33]. Based on these promising findings, we developed a challenging clinical trial using eye-tracking metrics as a surrogate outcome.

The COG-EYE study is quite different from previous clinical trials in MCI as it uses a challenging primary outcome. We aim to determine whether donepezil improves visuospatial function in patients with MCI. Moreover, it is expected that eye-tracking and digital pen data may provide helpful biomarkers for identifying subtle changes that are difficult to measure with conventional methods.

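### The primary outcome is an unsigned change in a fixation ratio, so the protocol never says which result would count as benefit

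*Protocol article*

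**What the plan says.** The Trial design section calls this a "superiority trial with a 1:1 allocation ratio to evaluate the efficacy of donepezil in improving visuospatial abilities in patients with MCI". The primary objective asks whether donepezil benefits visuospatial function, as assessed by eye-tracking. Both statements have a direction.

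The endpoint has none. Outcomes {12} gives "Changes in the ratio of the number of fixations between the two AOIs (working space/perceptual space) performed by the simplified RCFT", measured over the 12-week study, and the Abstract defines it in the same way. Sample size {14} uses a standardized effect of 0.8 without a sign, "using a two-sided two-sample" t-test at the 0.05 level. Statistical methods {20a} states: "The primary outcome will be analyzed using the two-sample" t-test, and then: "An analysis adjusting for the baseline value will also be performed for each outcome".

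The Discussion comes nearest to a direction. The group's own work suggested that "the increased number and duration of fixations might reflect more cognitive efforts to compensate for the lack of visual perception in patients with AD". Another cited study found that "fixation time and frequency were reduced on social images in apathetic patients with AD".

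The article also gives the primary test in different ways. Statistical methods {20a} names only the t-test for this outcome. The Abstract offers the t-test or the Mann–Whitney test for primary and secondary outcomes. Section {18a} adds a non-parametric option if parametric requirements fail.

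**The concern.** A superiority claim needs a better side. For MMSE or VOSP the better side is generally understood. For a new quotient of two fixation counts it is not. The ratio can rise because the participant looks less often at the model or because the participant fixates more on the drawing, and these need not mean the same thing for visuospatial ability.

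Participants, caregivers and all staff know the allocation, and section {16a} relies on this eye-tracking outcome, in place of clinical ratings, to limit bias. That protection is weakened if the meaning of a positive result can be settled after the arms have been compared. A significant p-value would then show that donepezil changes gaze behaviour, but not that it helps.

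**Working it through.** **1. The plan's own figure.** Inputs from Sample size {14}: effect 0.8, two-sided alpha 0.05, power 90%, attrition 12%. The noncentral-t calculation gives n = 33.83, so 34 per group, with power 90.2% at 34. Attrition: 34 / 0.88 = 38.6, so 39 per group and 78 in total. The arithmetic is right.

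**2. Is a direction stated anywhere?**
- Objective and Trial design: benefit, superiority.
- Abstract, Outcomes {12}, Sample size {14} and Statistical methods {20a}: change, two-sided, effect unsigned.
- Source of the 0.8: fixation frequency in apathetic versus non-apathetic AD. It is not a ratio, a change over time or a drug effect, so it supplies no sign for this endpoint.
- Discussion: one result on more and longer fixations, another on fewer fixations on social images in apathy. Neither concerns working/perceptual.

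No section supplies the sign.

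**3. Why it cannot be inferred.** A made-up participant has 40 working and 20 perceptual fixations: 40/20 = 2. With half the looks at the model, 40/10 = 4. With twice the fixations on the drawing, 80/20 = 4. The change is +2 in both cases, by different behaviour. Only the two separate counts tell them apart.

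**4. What the missing sign costs.** This step needs no assumption about spread.
- No true effect: the two-sided 5% test puts a nominal 2.5% in each tail (2.1% and 2.6% in a simulation of the raw ratio). If either tail may be read as improvement, the false-claim rate is 2.5% + 2.5% = 5%. If one side is named, it is 2.5%.
- True standardized effect of 0.8 in the unfavourable direction: by symmetry the test is significant about 90% of the time, and nothing in the text prevents it being presented as benefit.

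**5. Does the raw scale undermine the 90%?** The article gives no mean, SD or distribution for the ratio, so the spreads here are assumptions. Simulation: 34 per arm, log-normal ratios, baseline-to-week-12 correlation rho = 0.5 on the log scale.

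(a) Effect of 0.8 SD on the raw change, as an additive shift. This is the natural reading of {14}. Power is 89–91% in both directions at log-SD 0.1 to 0.7.

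(b) Multiplicative effect: 0.8 SD of the change in log ratio, lowering the ratio.

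| Assumed log-SD | t-test, raw change | t-test, log change | Baseline-adjusted, log |
|---|---|---|---|
| 0.1 | about 89% | about 90% | about 95–96% |
| 0.3 | about 83% | about 90% | about 95–96% |
| 0.5 | about 75% | about 90% | about 95–96% |
| 0.7 | about 65% | about 90% | about 95–96% |

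If the multiplicative effect raises the ratio, the raw t-test keeps about 86–92%.

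Check of the last column: the SD of the log change is s × √(2(1 − 0.5)) = s, where s is the log-SD. After baseline adjustment the residual SD is s × √(1 − 0.25) = 0.866s. The effect in residual-SD units is 0.8 / 0.866 = 0.92 in place of 0.8, which gives the higher power.

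**The case against.** The article condenses a full protocol that it says is supplied as supplementary material. Scale, transformation and the rule for claiming superiority are commonly left to an analysis plan. Two-sided testing is normal in a superiority trial, and VOSP and the planned correlations with cognitive scores would help to interpret the ratio. Most of this stands. The direction of benefit is different: it is part of the endpoint's definition, and a supportive correlation seen afterwards does not replace it.

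A reader might infer four stronger points that the documents do not support.
- *The 90% power is not delivered.* Section {14} places the 0.8 on the primary outcome itself, and on that reading 90% holds. A shortfall needs a multiplicative effect, a falling ratio and an assumed spread. Even then, the baseline-adjusted analysis on the raw scale, already planned as additional, has about 90–95% power at log-SD 0.3 to 0.7.
- *The result depends on which area is the denominator.* The Abstract and Outcomes {12} both fix working over perceptual, so nobody is free to invert it.
- *The article's evidence contradicts itself on direction.* The two Discussion results come from different tasks and constructs, and neither is about the ratio. The text is silent, not contradictory.
- *There is no non-parametric option for the primary outcome.* The Abstract and {18a} mention one. The fault is that they disagree with {20a}.

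**Conclusion.** The point holds for the direction of benefit. A directional objective is tied to an unsigned endpoint, and no section says which way is better. The consequence rests on no assumed variance: a 5% rather than 2.5% chance of a reportable improvement when there is no effect, and about a 90% chance of a significant result if the drug moves the ratio by 0.8 SD the wrong way.

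The scale of analysis is secondary. The sample size reproduces and is not shown to be wrong. The fall in power to between 89% and 65% is conditional on a multiplicative effect that lowers the ratio, at assumed log-SDs of 0.1 to 0.7 and rho 0.5. It is a reason to prefer the baseline-adjusted log ratio, not evidence of an error. If the unseen full protocol already names the direction, what remains is to bring the published definition into line with it.

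**What to change.** 1. In Outcomes {12}, state which direction of working/perceptual is improvement and justify it, for instance from the group's earlier eye-tracking data. Do this before database lock and, because the trial is open-label, before anyone compares the ratio by arm.
2. Claim superiority only if the 95% CI for the treatment difference lies wholly on the named side. The two-sided test can stay.
3. Report working-space and perceptual-space counts separately by arm, so that a change in the ratio can be traced to its source.
4. In Statistical methods {20a}, make the baseline-adjusted analysis primary, preferably on log(working/perceptual), back-transformed to a ratio of ratios. Pre-state a rule for zero counts, since the log is undefined there; adding 0.5 to both counts is one example. Keep the raw-change t-test as a sensitivity analysis.
5. Reconcile {20a} with the Abstract and {18a}, so that one primary test is named.

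Cost: recruitment is under way, so this is an amendment. Section {25} sends important changes to the regulator and the IRB and has approved ones communicated to the registry. Results would be read as percentage differences in place of raw ratio units. No extra participants, visits or measurements are needed.
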